### Interim analyses {21b}

We have no plans to conduct any interim analyses since both interventions are associated with a low degree of risk.

### Method for additional analyses (e.g., subgroup analyses) {20b}

Subgroup analyses will be performed for the surgical approach (laparotomy or laparoscopy). *P* values of < 0.05 will be considered statistically significant.

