In gastroenterological surgery, MAWIs are widely used because they enable access to the whole abdominal cavity in open surgery. With the development of surgical technology since the 1990s, surgical procedures have progressed from open surgery to minimally invasive surgery, such as laparoscopic surgery and robotic surgery. With current surgical practices in developed countries, the proportion of minimally invasive surgery among gastroenterological surgeries is reported to be approximately 70% [15, 16]. Minimally invasive surgery has been revealed to reduce IH as an SSI [4]. However, the use of an MAWI as a specimen extraction site was found to be associated with a higher incidence of IH in comparison to nonmidline incision sites [4]. An MAWI is most frequently used as a site for specimen extraction in minimally invasive surgery because it achieves better cosmesis; thus, the development of an ideal method for MAWI closure after gastroenterological surgery is necessary for both open and minimally invasive surgery.

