### Sample size {14}

A retrospective cohort of patients who underwent gastrointestinal surgery and MAWI closure (in which the peritoneum and fascia were sutured together using interrupted sutures with 1-PDS plus, with subcutaneous interrupted sutures then used for skin closure using 4–0 PDS) at our department from June 2019 to December 2020 was analyzed. The incidence rates of each complication were as follows: incisional SSI (7.6%), hematoma (5.1%), 5.9% seroma (5.9%), superficial dehiscence (1.4%), total dehiscence (0%), and IH at approximately 1 year after surgery (16.8%). When a patient developed more than 2 wound complications, the number of patients who developed wound complications was assumed to be one. In total, the incidence of wound complications was 29.2%. In this trial, we hypothesized that midline abdominal wall incision closure with continuous suturing of the fascia using a single-layer aponeurotic technique and continuous suturing of the subcuticular tissue would achieve a 50% reduction in the incidence of wound complications. The expected wound complication rates of the study and control groups were 14.6% and 29.2%, respectively. Power and Sample Size Calculation version 3.1.6 was used for sample size estimation [21]. With a two-sided alpha level of 0.05, it is estimated that a total of 250 patients will be needed for the trial to have 80% power to detect superiority in the reduction of the frequency of wound complications. Two percent of cases are expected to be excluded after allocation, and 10% of cases are expected to drop out during the postoperative follow-up period. Thus, the total target number of cases is set at 284 (Fig. 1).

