## Assignment of interventions: allocation

### Sequence generation {16a}

Participants will be registered, randomized, and allocated by nonblinded investigators. Participants’ data will be password-protected and will only be accessible by investigators. All access to the secure separate database will be monitored and logged. Permuted-block randomization with an allocation ratio of 1:1 and blocking will be used. The randomization will be stratified by sex, surgical organ (upper gastrointestine, small bowel, colorectum, hepatobiliary–pancreas, and others), and surgical approach (laparotomy or laparoscopy).

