## Statistical methods

### Statistical methods for primary and secondary outcomes {20a}

All analyses will be performed after the termination of the main part of the trial, that is, after the last 1-year follow-up visit has taken place. We will perform the primary analyses using the full analysis set, from which patients who do not undergo surgery or who withdraw their consent before the assessment of the primary endpoint are excluded (modified intention-to-treat set). In addition, we will repeat the analyses in the per-protocol set, further excluding patients with major protocol deviations. Student’s *t* test or the Mann–Whitney *U* test will be used to compare continuous variables with a normal or nonnormal distribution. The *χ*^2^ test or Fisher’s exact test will be used to compare categorical variables between the study group and the control group. *P* values of < 0.05 were considered to indicate statistical significance. All statistical analyses will be conducted using EZR [23].

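### The P < 0.05 rule for subgroups by surgical approach most naturally means a separate test within each approach, which cannot show whether the effect differs between laparotomy and laparoscopy

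*Protocol article*

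**What the plan says.** The section on additional analyses {20b} has two sentences. The first states that "Subgroup analyses will be performed for the surgical approach (laparotomy or laparoscopy"). The second states that P "values of < 0.05 will be considered statistically significant".

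The section does not say which P value the threshold governs. The statistical methods section {20a} gives the only test for a binary outcome, a χ² or Fisher's "exact test will be used to compare categorical variables between the study group and the control group". That is a between-arm test.

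The trial is sized for the whole sample only: "With a two-sided alpha level of 0.05, it is estimated that a total of 250 patients will be needed" for "80% power to detect superiority in the reduction of the frequency of wound complications". Surgical approach is one of the stratification factors in the sequence generation section {16a}, and allocation is 1:1.

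**The concern.** A subgroup analysis by approach asks whether the benefit of the study closure differs between open and laparoscopic surgery. That is a comparison of two treatment effects. A between-arm P value within each approach asks something else, namely whether each effect on its own can be told apart from zero. The answer depends heavily on how many patients fall in each approach. In a trial with 80% power overall, each part has clearly less.

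The likely product of such a rule is a statement that closure works in one approach and not in the other, when the data show no such difference. The background argues that a good midline closure is needed for both open and minimally invasive surgery, and the discussion hopes to inform guideline updates. A spurious contrast by approach would therefore bear directly on the use the authors foresee. The two tests also add two further 5% chances of a positive claim when there is no effect.

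**Working it through.** **Inputs from the protocol article.** Sample size {14}: "The expected wound complication rates of the study and control groups were 14.6% and 29.2%, respectively"; two-sided alpha 0.05; 250 evaluable; losses of 2% and 10%. Sequence generation {16a}: "Permuted-block randomization with an allocation ratio of 1:1 and blocking will be used", stratified by approach, so the arms are taken as equal within each approach.

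**Assumption.** The split between approaches in this trial is not given. The background reports that "the proportion of minimally invasive surgery among gastroenterological surgeries is reported to be approximately 70"%, but this describes practice in developed countries in general. Splits from 50/50 to 80/20 are therefore shown.

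**1. The plan's own figure.** With mean rate 0.219 and difference 0.146:

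n per arm = [1.96·√(2·0.219·0.781) + 0.8416·√(0.292·0.708 + 0.146·0.854)]² / 0.146² = 124.8, so 125 per arm and 250 in total. Inflation: 250/(0.98·0.90) = 283.4, so 284. Both stated figures reproduce. Power at 125 per arm is 80.1%.

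**2. Power within one approach.** With n patients per arm in that approach:

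power = Φ[(0.146 − 1.96·s0)/s1], where s0 = √(2·0.219·0.781/n) and s1 = √((0.292·0.708 + 0.146·0.854)/n).

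Example for 70/30:
- Larger approach, n = 87.5: s0 = 0.0625, s1 = 0.0615, power 65%.
- Smaller approach, n = 37.5: s0 = 0.0955, s1 = 0.0940, power 33%.

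**3. Same true effect in both approaches.** With powers A and B, exactly one is significant with probability A(1−B) + B(1−A). For 70/30 this is 0.648·0.669 + 0.331·0.352 = 0.55.

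| Split | Power, larger / smaller | Exactly one | Both | Neither |
|---|---|---|---|---|
| 50/50 | 50% / 50% | 50% | 26% | 24% |
| 60/40 | 58% / 42% | 51% | 25% | 24% |
| 70/30 | 65% / 33% | 55% | 21% | 24% |
| 80/20 | 71% / 24% | 61% | 17% | 22% |

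Exact enumeration of the χ² test gives 50%, 51%, 56% and 61% for exactly one. Fisher's test gives 49%, 50%, 54% and 61%. With all 284 evaluable, the range is 49% to 63%.

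**4. Given a significant overall result.** By simulation (400,000 trials), exactly one approach is significant in 57%, 59%, 63% and 71% for the four splits.

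**5. Smaller uniform effect, 250 patients, splits 50/50 and 70/30.**
- Study-group rate 17.5% (a 40% reduction): exactly one in 45% to 47%, neither in 43% to 44%.
- Study-group rate 20.4% (a 30% reduction): exactly one in about 32% to 34%, neither in about 62% to 64%.

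**6. No effect at all.** At least one significant: 1 − 0.95² = 0.0975, about 10%.

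**7. The alternative.** In the same simulation, an interaction test on the log odds ratio at two-sided 0.05 wrongly signals a difference in 3% to 4% of trials with a uniform effect. To gauge its power, suppose the effect lies only in the larger approach. The difference in log odds is then ln(0.292/0.708) − ln(0.146/0.854) = 0.881. Its standard error is √Σ 1/(n·p·(1−p)) over the four cells, which is 0.600 at 50/50 and 0.718 at 80/20. Power = Φ(0.881/0.600 − 1.96) = 31% and Φ(0.881/0.718 − 1.96) = 23%.

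**The case against.** The best defence is that {20b} never says the P value is a within-approach one. It could be an interaction P value, and a full protocol or SAP that is not shown may say so. This stands as a limit on certainty: separate testing is the natural reading, not an explicit statement. For the same reason, the absence of an interaction test from a condensed article is not the finding. The finding is the significance rule that the article does state. The only test it can be joined to is the between-arm test in {20a}.

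A reader might infer that a uniform effect would usually look confined to one approach. The figures do not support this in general. The chance is 50% at an even split and falls to about a third if the true reduction is 30%, when the commonest result is neither approach significant. It is clearly above half only with an uneven split or given a positive overall result. Nor can 70/30 be taken as this trial's split.

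A reader might also infer that the authors plan to claim a difference by approach, or that the primary test's error rate is affected. Neither follows. The objective concerns overall incidence, approach is a single prespecified factor that is also a stratifier, and the primary comparison is untouched. These points limit the severity. They do not make two separate P values an answer to the subgroup question.

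**Conclusion.** The point holds as a defect in a stated rule for a supporting analysis. On the natural reading, the article declares subgroup significance from separate 5% between-arm tests, and these cannot show whether the effect differs by approach. If the planned effect is the same in both approaches and 250 patients are evaluable, the chance that exactly one approach is significant is about 50% to 61% over assumed splits of 50/50 to 80/20, and both are significant in only 17% to 26%. With no effect, at least one is significant in about 10%.

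These figures rest on the design's event rates holding in both approaches, equal arms within each, and an assumed split. They fall if the true effect is smaller than planned. The rule should be changed before analysis; the primary result does not depend on it.

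**What to change.** Replace the P < 0.05 sentence in {20b} with text of this kind: *Whether the treatment effect differs by surgical approach will be judged from the treatment-by-approach interaction, reported as an estimate with 95% CI and P value, from a model containing treatment, approach as stratified at randomization, and their product. The risk difference with 95% CI will be shown for each approach as exploratory, and no claim of significance will be made within an approach.* State the scale of the interaction (for example, odds ratio or risk difference) in advance.

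The article specifies no adjusted model for the primary outcome, so this adds one simple regression model to the plan. It needs no new data, because approach is already recorded for stratification, and all analyses follow the last 1-year visit. The price is fewer subgroup claims and a test with low power, about 23% to 31% even if the whole effect lay in the larger approach. The text should therefore also say that a non-significant interaction is not evidence of equal effects.

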### Methods in the analysis to handle protocol nonadherence and any statistical methods to handle missing data {20c}

If missing data for any variable exceed 5%, multiple imputations will be used to handle missing values.

### Plans to give access to the full protocol, participant-level data, and statistical code {31c}

The collection of data underlying this article is in progress. When data collection and follow-up are finalized, data from the study will be available on reasonable request from the corresponding author.

## Oversight and monitoring

### Composition of the coordinating center and trial steering committee {5d}

The authors will coordinate and steer this study.

### Composition of the data monitoring committee, its role, and reporting structure {21a}

We do not have the composition of the data monitoring committee. During the study period, data monitoring and surgical monitoring for this trial will be conducted by blinded investigators who are not participating in this trial.

### Adverse event reporting and harms {22}

Adverse effects can be part of the outcome measures detailed earlier in the protocol or other unspecified side effects. MAWI closure with continuous or intermittent suturing of the fascia and subcutaneous tissue is generally performed in daily surgical practice. STRATAFIX SYMMETRIC PDS plus, 4–0 STRATAFIX Spiral PDS plus, PDS plus, and 4–0 PDS plus (Ethicon, Johnson & Johnson, Somerville, New Jersey, USA) are used in a manner that is in line with the Pharmaceutical Affairs Law.

Adverse events cover any signs, symptoms, syndrome, or illness that appears or worsens in a patient during the observation period in the clinical trial and that may impair the wellbeing of the patient. Any adverse events that require additional pharmacological, interventional, or surgical management within the study periods will be collected by non-blinded investigators and monitored by blinded investigators who are not participating in this trial. Adverse events will be regarded as postoperative complications and graded according to the Clavien-Dindo classification [24]. A serious adverse event is any adverse event that occurs at any time during the observation period that results in death, is immediately life-threatening, requires or prolongs hospitalization, results in persistent or significant disability or incapacity, or causes congenital anomalies in offspring. Each participant will receive informed consent about notification and follow-up of adverse events and will be provided with medical care for any potential harm stemming from their participation in the trial. Documentation and relevant patient data on all serious adverse events will be submitted to the Bioethics Committee for Clinical Research, Saitama Medical Center, Jichi Medical University, and the committee will decide on the final diagnostic classification of critical clinical events and make recommendations on whether this trial should be stopped or not.

### Frequency and plans for auditing trial conduct {23}

The progress of the trial will be updated on the web page of UMIN-CTR every 6 months, and the Bioethics Committee for Clinical Research, Saitama Medical Center, Jichi Medical University will monitor progress approximately every year. All data will be collected by the investigators in an anonymous and encrypted database. The confidentiality of the participants will be maintained at all times. The investigator will maintain all study-related information, including medical records, CRFs, written informed consent documents, and other pertinent data, for 5 years after trial termination.

### Plans for communicating important protocol amendments to relevant parties (e.g., trial participants, ethical committees) {25}

If the protocol needs to be modified, it will be reviewed again by the ethics committee, and upon approval, the trial registry and protocol will be updated.

### Dissemination policy {31a, 31b}

The final results will be reported in international peer-reviewed journals immediately after the completion of the trial. All authorships will be in accordance with the International Committee of Medical Journal Editors guidelines. We do not intend to use professional writers.

## Discussion

This study is designed to establish the ideal combination of fascial and skin closure of a clean-contaminated MAWI wound after gastroenterological surgery for reducing the incidence of overall wound complications. No previous studies have evaluated the ideal combination of fascial and skin closure of MAWI.

High-quality studies adhere to methodological principles to minimize errors in surgical trials, including adequate randomization, concealment of allocation, blinding, performance of an intention-to-treat analysis, complete follow-up, reliable accurate outcome measures, and an a priori sample size calculation [25]. The present trial is designed according to these principles. Our inclusion and exclusion criteria for participants aim to select homogenous patients with clean-contaminated wounds. The primary outcome of this trial is the incidence of wound complications, including subcutaneous hematoma, seroma, incisional SSI, wound dehiscence, and IH. Incisional SSI is defined according to the standard criteria devised by the CDC, which have been used for research, quality improvement, public reporting, and pay-for-performance comparisons; the definition is considered the most reliable [18]. IH is defined according to the European Hernia Society guidelines, either clinically or by imaging [19]. CT is reliable and reproducible, and therefore, the inclusion criteria demand that patients are scheduled to undergo CT 1 year after surgery [3, 4, 19]. Thus, reliable accurate outcome measures are used. In the retrospective cohort of patients used for the calculation of the target number of this trial, SSI and IH are also judged using these definitions. The incidence rates of hemorrhage or hematoma, incisional SSI, seroma, wound superficial or complete dehiscence, and IH in a retrospective cohort are almost equal to the general incidence rates [1–4, 7–14]. There have been no studies evaluating the ideal combination of fascial and skin closure of MAWIs for reducing the incidence of wound complications. Therefore, we hypothesized that MAWI closure with continuous suturing of the fascia using a single-layer aponeurotic technique and continuous suturing of the subcuticular tissue achieves a 50% reduction in the incidence of wound complications because it is clinically meaningful in patients undergoing elective gastroenterological operations. In addition, the number of dropout cases was predicted based on two previous RCTs conducted by our department [16, 26, 27] and the protocols of previous RCTs for MAWI closure [28–30]. Thus, the total number of cases might be as accurate as possible. As 50–70% of IHs occur within 1 year after the operation, we decided that the postoperative follow-up period would be 1 year, and the incidence of IH at this time was the primary end-point of this trial [28–30]. Because this RCT was conducted in a single center, the follow-up of outcomes can be expected to be more complete in comparison to multicenter RCTs.

In this trial, multiple perioperative measures for SSI prevention are implemented according to clinical guidelines [31, 32]. The implementation of a set of evidence-based practices for the prevention of SSI has been proven to reduce the incidence of incisional SSI in gastroenterological surgery [33]. Recent studies have shown that the small bite technique for MAWI closure is effective for the prevention of IH. These studies were of acceptable quality; thus, the technique has been incorporated into the updated guidelines [4, 34–36]. In addition, the implementation of the small bite technique for MAWI closure in clinical practice may be correlated with a reduction in incisional SSI [37, 38]. Irrespective of the applied suture technique, slowly absorbable sutures were revealed to be associated with a significantly lower incidence of IH in the INLINE study [39]. Therefore, the small bite technique using slowly absorbable sutures is implemented in both groups. The efforts in this trial might determine the precise incidence of wound complications under appropriate management based on the current guidelines.

The present study is associated with some limitations. First, it includes all patients undergoing gastroenterological surgery, regardless of the organ, diagnosis, or procedure. Second, the trial is conducted in a single center, and single-center RCTs typically show greater treatment effects than multicenter RCTs [25]. A well-designed multicenter RCT will be needed to generalize and demonstrate the results of this study.

In conclusion, this trial will provide initial evidence on the ideal combination of fascial and skin closure for MAWI to reduce the incidence of overall postoperative wound complications after gastroenterological surgery with a clean-contaminated wound. This trial is expected to generate high-quality evidence that supports the current guidelines for the closure of abdominal wall incisions from the European and American Hernia Societies and to contribute to their next updates.

### Protocol version and trial status {3}

Recruitment is continuing steadily, and as of December 25, 2023, 154 participants have been enrolled. The current protocol is in operation at version 1.2 (January 4, 2023). Recruitment is expected to end in December 2024.

## Data Availability

Deidentified participant data that underlie the results reported in this article will be made available to researchers who provide a methodologically sound proposal. Proposals should be directed to [name] ([contact]); to gain access, data requestors will need to sign a data access agreement.
